### Expected adverse events

Due to the benign nature of the physical activity intervention, no serious adverse events are anticipated. However, the following non-serious expected adverse events, typically associated with increased physical activity, may occur and will be recorded in the Case Report Form:
•Delayed Onset Muscle Soreness (DOMS)•Mild fatigue

An
**Unexpected Adverse Event** is defined as an event whose nature or severity is not consistent with expected outcomes of the intervention and is not listed in the protocol as an expected AE.

Participants in the intervention group will be instructed to contact the research team if they experience any AEs during the study. In addition, at each exercise session, participants will be asked whether they have experienced any AEs since their last contact.

All reported adverse events will be documented. The seriousness, expectedness, and causality of each event will be assessed by the research team.

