## Intervention group: Online exercise and education programme

The intervention is an 8-week online exercise and education programme consisting of an online exercise class once per week, in accordance with exercise prescription guidelines for people with CP.
^7^ The programme will consist of eight weekly group sessions, each lasting 60 minutes. Each session will include (i) 5–8 minutes for warm-up, a 30 minute exercise programme, 5 minutes for cool-down, and (ii) 15–20 minutes of interactive learning focused on a topic of relevance to adults with CP.

The online exercise class will focus on mobility, strength and balance exercises for major muscle groups, based on the most common reasons that adults with CP seek physiotherapy.
^15^ Balance will be both explicitly targeted and integrated within functional exercises throughout the programme. Participants will complete up to 10–11 exercises in each class. In standing, balance will be challenged through functional tasks such as sit-to-stand, squats, side stepping, toe taps and exercises involving weight shifting or changes in base of support. The exercises may be completed in sitting or standing depending on the person’s ability. For participants exercising in sitting, balance will be addressed through trunk control and postural stability activities, such as unsupported sitting, reaching tasks, and dynamic upper limb movements performed within a safe and supported environment. The intervention will be tailored to individual ability, with exercises adapted based on mobility level (GMFCS I-V), upper limb function, associated impairments (e.g. communication, vision, or hearing) and risk assessment findings, while maintaining a consistent overall structure. Where required, participants may be supported by a family member or caregiver to assist with communication, technology use, or safe participation. Participants will complete between 2 and 4 sets of 6–15 repetitions of each exercise. Exercises will focus on functional, task-oriented movements targeting mobility, strength, and balance. The programme will emphasise controlled, submaximal effort and movement quality rather than maximal or high-velocity (power-based) training. Exercise intensity will be individualised and guided by participant ability, with participants encouraged to work at a moderate level that is challenging but safe.

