Participants will also be encouraged to repeat the exercises independently twice per week between sessions. Participants will be provided with access to private exercise videos demonstrating the exercises performed during the online sessions to support independent completion. Adherence to the intervention will be recorded through attendance at online sessions and a brief self-reported survey capturing whether participants completed the prescribed exercises independently at least twice per week. The number of sets and repetitions performed during supervised sessions will also be recorded, with progression guided by participant ability over the 8-week programme. Progression will be achieved by modifying repetitions, sets, range of movement, level of support, and exercise complexity, rather than through one-repetition maximum testing. Examples of exercises include overhead reach, Table or box push-ups, Lateral arm raises, Knee up, hip back or wheelchair dip, side step or hip out, sit to stand, squat, knee straight/bend, heel raises and seated rowing as well as balance-focused activities such as weight-shifting and reaching tasks. For example, exercises such as squats may be performed in standing with or without support or adapted to seated alternatives (e.g., sit-to-stand or wheelchair-based upper body movements) to accommodate different mobility levels. Exercises will be demonstrated with options and progressions to enable participation within a group setting while accommodating individual differences. Verbal cueing and demonstration will be used to guide correct technique, pacing, and safe execution of movements during each session.

The 15–20 minute interactive learning component of each weekly online class will consist of educational materials on exercise, nutrition, mobility changes, fatigue, optimising bone health, pain management, mental health, sleep and physical activity maintenance (one topic per week). Educational materials and exercises will be delivered during the online class. The educational content is consistent across both study groups; however, in the intervention group it is delivered interactively during weekly sessions.

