### Assessments

All participants will complete self-reported assessments at baseline (0 weeks) and immediately after participation in the eight week programme. Assessments may be completed online, on the phone, in person with the post-doctoral research fellow or on paper. Participants who complete paper versions will be given a freepost envelope to return the completed forms. The online outcome measures will be hosted on REDCap, an online survey platform.

The following data will be collected at baseline only:

1. Socio-demographic
a.Ageb.Gender

2. Condition-specific information
a.Type of CPb.GMFCS levelc.Intellectual disabilityd.Secondary impairments

The data shown in
Table 3 will be collected at baseline and follow-up:

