### Implementation

Implementation will be assessed by recording:
•Attendance at sessions to evaluate fidelity to intervention receipt.•Self-reported completion of the prescribed exercise programme to evaluate fidelity of intervention content. Participants in the intervention group will complete a brief weekly survey indicating whether they completed the prescribed exercises independently at least twice per week in addition to the supervised session.

Practicality will be assessed by recording adverse events reported by participants in both groups at each assessment time point.

**An Adverse Event (AE)** is defined as any untoward medical occurrence affecting a participant that does not necessarily have a causal relationship with the intervention (
https://www.ct-toolkit.ac.uk/glossary).

**A serious adverse event (SAE)** is defined untoward medical occurrence/effect that:
(a)results in death;(b)is life-threatening;(c)requires hospitalisation or prolongation of existing hospitalisation;(d)results in persistent or significant disability or incapacity.

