### Withdrawals

Participants who withdraw prior to commencing the intervention will continue to receive standard usual care, defined as any healthcare, physiotherapy, exercise, or community-based services they would typically access independently as part of their routine care. Participants will not be instructed to modify or discontinue any existing care or physical activity during the study. Participants will be encouraged to allow data that have been collected before withdrawal to be used in the analyses. However, if consent to use data is also withdrawn, then these will be discarded. Participant withdrawals will be recorded in a Change of Status form. Participants who withdraw will not be replaced.

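### The weekly adverse-event question in the intervention arm is asked only at classes, so events that lead to absence or drop-out may be under-ascertained or recorded late

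*Protocol article*

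**What the plan says.** The protocol article describes these routes for adverse events.

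- **Class question, intervention arm** (Expected adverse events): "at each exercise session, participants will be asked whether they have experienced any AEs since their last contact". There are eight occasions: "The programme will consist of eight weekly group sessions, each lasting 60 minutes".
- **Self-report, intervention arm** (same section): "Participants in the intervention group will be instructed to contact the research team if they experience any AEs during the study".
- **Assessments, both arms** (Implementation): "Practicality will be assessed by recording adverse events reported by participants in both groups at each assessment time point". The section Assessments gives two time points: "All participants will complete self-reported assessments at baseline (0 weeks) and immediately after participation in the eight week programme".

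Two further contacts matter here. Under Implementation, "Participants in the intervention group will complete a brief weekly survey"; its described content is whether the home exercises were done at least twice that week. Under Withdrawals, "Participant withdrawals will be recorded in a Change of Status form"; the items on that form are not given.

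Exercise also takes place away from class: "Participants will also be encouraged to repeat the exercises independently twice per week between sessions". In Table 1, recording of adverse events is the only outcome listed for practicality.

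**The concern.** Whether a participant is actively asked about adverse events in a given week depends on being in class that week. The Background names pain, fatigue and a rising risk of falls as common in this population, and any of these can keep someone at home. Enquiry is then thinnest among people who may be absent because something happened to them.

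The stake is the practicality domain, which rests on the number and type of events and feeds the decision on a larger trial. Events that stop people taking part are the most informative ones for that decision. The article records attendance, the number and proportion who drop out, and reasons for exclusion or for declining to join. It states no reason for a missed class or for drop-out. If some absence were caused by events, the data as described might not separate it from loss of interest.

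**Working it through.** The protocol states no event rate, attendance rate, drop-out rate or precision target for adverse events, so there is no figure of its own to reproduce. The check has three parts.

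**1. Scheduled enquiries after baseline, per participant**

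| Situation | Class question | Week 8 | Total |
|---|---|---|---|
| Intervention, attends all classes | 8 | 1 | 9 |
| Intervention, attends k classes | k | 1 | k + 1 |
| Intervention, attends none | 0 | 1 | 1 |
| Control | 0 | 1 | 1 |

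If the week-8 assessment is also missing, the total falls to k.

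**2. Weeks without a same-week question**

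With 30 intervention participants and 8 weeks there are 30 × 8 = 240 person-weeks. Attendance is an assumption:

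- 90%: 0.10 × 240 = 24 unprompted person-weeks
- 70%: 0.30 × 240 = 72
- 60%: 0.40 × 240 = 96

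These are weeks without a prompt. They are not lost events.

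**3. How far the other routes limit permanent loss (illustration; every rate is assumed)**

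Let q be the share of events that cause absence, s the chance of self-report, r the chance of returning to a later class and reporting there, and w the chance of capture at week 8. Treating these as independent, the share of all events lost is q(1 − s)(1 − r)(1 − w).

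| s, r, w | q = 0.1 | q = 0.3 |
|---|---|---|
| 0, 0, 0 (no backup works) | 10% | 30% |
| 0.3, 0.3, 0.5 | 0.1 × 0.7 × 0.7 × 0.5 = 2.5% | 7.4% |
| 0.5, 0.5, 0.7 | 0.1 × 0.5 × 0.5 × 0.3 = 0.8% | 2.3% |

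The average hides where the loss sits. For someone who never returns, r = 0. With s = 0.3 and w = 0.5, the chance that the event is lost is 0.7 × 0.5 = 35%. If that person also gives no week-8 assessment, w = 0 and it is 70%.

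The effect on seeing any event at all is modest. With 30 participants the chance of at least one recorded event is 1 − (1 − p(1 − m))^30, where p is the true risk per participant and m the share lost.

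| True risk p | m = 0 | m = 5% | m = 30% |
|---|---|---|---|
| 10% | 95.8% | 95.0% | 88.7% |
| 5% | 78.5% | 76.8% | 65.7% |

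**The case against.** The strongest reply is that absentees are not beyond reach. The class question looks back to the last contact, so an event in a missed week, or during home exercise, is asked about at the next class attended. Intervention participants are told to report any event themselves. The week-8 assessment does not depend on attendance and can be done online, by phone, in person or on paper. Stopping classes is not withdrawal from the study, so a non-attender is still due that assessment. All of this stands. A reader might infer that absentees are never asked, or that harm will be under-counted; the documents support neither.

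A reader might also take the Withdrawals section to rule out learning about an event at exit. It asks for permission to use data already collected and does not bar a question at withdrawal.

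Finally, the weekly survey, the Case Report Form and the Change of Status form are named but not shown, and an article may leave form items to the full protocol. This stands for the Change of Status form, which may already ask for the reason. It has less force for the weekly question. The article sets out who is asked, when and by which route, and describes the survey separately with a different purpose. The point is therefore about a stated collection scheme and not about omitted detail.

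What the reply does not remove is that self-report is passive, look-back fails for those who do not return, and week 8 relies on recall over as much as eight weeks and on the assessment being completed.

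**Conclusion.** The point holds as a risk of under-ascertainment or late recording within the intervention arm. Scheduled active enquiry varies from 1 to 9 with attendance, and attendance can be lowered by the events being counted. The exposed group is mainly people who stop attending, do not self-report and give no week-8 assessment; minor events forgotten by week 8 are a lesser part. The loss cannot be sized from the documents, and the percentages above only show how it responds to assumed rates.

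Two stronger conclusions might be drawn and are not supported. One is that the unprompted person-weeks measure missed harm; look-back and week 8 can recover events from them. The other is that the scheme makes the intervention look safer than control. With up to 9 enquiries plus an instruction to self-report, against 1 scheduled enquiry in control, the stated scheme would if anything tend to show relatively more events with the intervention.

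This is a worthwhile low-cost improvement to the sole practicality metric. It is not a flaw that invalidates it. It rests on the scheme as the article describes it; a full protocol that already follows up non-attenders would answer it.

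**What to change.** - Add to the weekly survey an adverse-event item and a reason-for-non-attendance item (for example health event, pain, fatigue, fall, other). Send the survey to every intervention participant each week, whether or not they attended.
- Keep the class question as an extra route. Reconcile the sources so that each event is counted once.
- Record on the Change of Status form whether an adverse event was the reason for withdrawal, if the form does not already do so.
- Compare event counts between arms only on the week-8 enquiry common to both. Report events found through the weekly routes descriptively for the intervention arm.

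If surveys are returned, the survey and week 8 together give 8 + 1 = 9 scheduled enquiries whatever the attendance, in place of 1 to 9.

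The cost is two items in a survey already in use and perhaps one line on an existing form. Participant burden rises slightly, the reported event count will be somewhat higher, and the gap in enquiry frequency from the control arm widens. That last effect is why the between-arm comparison should be limited to week 8.

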### Randomisation

Following the baseline assessment, participants will be randomly allocated to either an intervention or control group in a 1:1 ratio. Stratification will be based on their mobility status: GMFCS Level I-III (with or without walking aids) and GMFCS Levels IV-V (who use wheelchairs). The random allocation will be generated by a computer in random permuted blocks of 2 or 4, and implemented automatically within REDCap (Research Electronic Data Capture). Allocation concealment will be ensured as the sequence is embedded within REDCap and not accessible to the research team prior to assignment.

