### Control group

Participants allocated to the control group will receive the same educational materials as those in the intervention group. The educational content is consistent across both groups; however, in the intervention group it is delivered interactively within supervised sessions, while in the control group it is provided in a self-directed format. These will cover topics including exercise, nutrition, mobility changes, fatigue, optimising bone health, pain management, mental health, sleep and physical activity maintenance. These materials will be delivered weekly via email over the 8 week study period. Participants in the control group will not be prescribed a structured exercise programme during the study period. Following completion of the 8-week programme, participants in the control group will receive access to the same exercise videos and will be offered the opportunity to take part in an optional online exercise class.

Participants in both groups will be asked to continue their usual activities and will not be instructed to modify or stop any existing physical activity. The intervention is described in accordance with the TIDieR (Template for Intervention Description and Replication) checklist to support replicability.
^29^

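### Adverse events are asked about at weekly sessions in the intervention arm but, as far as stated, only once after randomisation in controls, so counts in the two groups are not directly comparable

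*Protocol article*

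**What the plan says.** Counting adverse events and describing their type is a listed objective, and recording them is the only measure given for the practicality domain (Protocol article, Table 1).

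- **Both arms.** Under Implementation: "Practicality will be assessed by recording adverse events reported by participants in both groups at each assessment time point". Under Assessments there are two such time points: "All participants will complete self-reported assessments at baseline (0 weeks) and immediately after participation in the eight week programme".
- **Order of events.** Under Randomisation: "Following the baseline assessment, participants will be randomly allocated to either an intervention or control group in a 1:1 ratio". The baseline time point therefore comes before any exposure.
- **Intervention arm only.** Under Expected adverse events: "Participants in the intervention group will be instructed to contact the research team if they experience any AEs during the study". The same paragraph adds that "at each exercise session, participants will be asked whether they have experienced any AEs since their last contact". The number of sessions is fixed: "The programme will consist of eight weekly group sessions, each lasting 60 minutes".
- **Control arm.** The described contact is emailed education material: "These materials will be delivered weekly via email over the 8 week study period". No adverse-event question is described with it. The optional exercise class for controls comes after the eight weeks.

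The definition of an adverse event under Implementation does not require a causal link to the intervention.

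**The concern.** The protocol records adverse events in both groups, but one group is asked far more often and over shorter recall periods. Because the definition ignores cause, ordinary background events count. The Background section says that pain, fatigue and falls are common in adults with CP as they age, and mild fatigue is also listed as an expected event of the programme. The same complaint can therefore be background or a consequence of exercise, and the concurrent control group is the natural way to tell them apart.

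That contrast is weakened if mild events in controls go unrecorded because nobody asked near the time. An excess in the exercise arm would then mix any effect of exercise with the effect of closer questioning. The results are meant to inform progression to a larger trial, and no later analysis can recover control events that were never elicited.

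**Working it through.** The protocol states no adverse-event rate, so there is no figure to reproduce. The check has two parts: a count of enquiries from the text, and an illustration under stated assumptions.

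**1. Enquiries after randomisation**

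- Intervention: 8 weekly sessions + 1 assessment at week 8 = up to 9, plus a standing instruction to report.
- Control: 2 assessment time points − 1 before randomisation = 1, with an eight-week recall period. No reporting instruction is stated.

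**2. Illustrative effect on recorded events**

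From the document: 30 participants per arm and 8 weeks. Assumed, not in the document: a true rate λ of 0.05 to 0.20 events per person-week, equal in both arms; recall that decays exponentially with half-life h of 2, 4 or 8 weeks, or does not decay; and attendance of 100% or 70%. The eighth session is taken to coincide with the week-8 enquiry. The standing instruction to report is left out of the model.

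With k = ln 2 / h and events spread evenly over time, the expected share of events recorded by an enquiry that looks back T weeks is

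c(T) = (1 − e^(−kT)) / (kT).

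At full attendance T = 1 for the intervention arm; T = 8 for controls. For h = 4, k = 0.1733:

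- Intervention: (1 − 0.841) / 0.1733 = 0.92
- Control: (1 − 0.25) / 1.386 = 0.54
- Ratio: 1.70 (from unrounded values)

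At 70% attendance, an event waits for the next attended session, and the week-8 enquiry is certain.

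| Recall half-life | Share recorded, intervention (full attendance) | Share recorded, control | Ratio, full attendance | Ratio, 70% attendance |
|---|---|---|---|---|
| 2 weeks | 0.85 | 0.34 | 2.50 | 2.26 |
| 4 weeks | 0.92 | 0.54 | 1.70 | 1.61 |
| 8 weeks | 0.96 | 0.72 | 1.33 | 1.29 |
| Perfect recall | 1.00 | 1.00 | 1.00 | 1.00 |

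The ratio does not depend on λ; the counts do. Expected recorded events per arm are 30 × 8 × λ × c, and the proportion of participants with any recorded event is 1 − e^(−8λc). For h = 4 and full attendance:

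| λ per person-week | True events per arm | Recorded, intervention v control | Any recorded event, intervention v control |
|---|---|---|---|
| 0.05 | 12 | 11.0 v 6.5 | 31% v 19% |
| 0.10 | 24 | 22.0 v 13.0 | 52% v 35% |
| 0.20 | 48 | 44.1 v 26.0 | 77% v 58% |

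**3. Same schedule in both arms**

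With the same T in both arms and full response, c(T) is equal and the expected ratio is 1.00 for any half-life.

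**The case against.** The strongest reply is that the protocol does not treat adverse events as a comparative endpoint. The objective is descriptive, Table 1 speaks only of recording, and the quantitative analysis section states no between-arm contrast and no threshold. Close weekly questioning of people who are exercising is good practice, and it makes their own event profile more complete. This stands. A reader might infer that the safety data cannot be interpreted; the documents do not support that, because the intervention-arm description is sound.

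Three further points have some weight.

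- **Other routes in controls.** All participants receive a leaflet with the researchers' contact details, and every reported event is to be documented whatever the arm. The leaflet is not shown. A reader might infer that controls have no way to report before week 8, but the text shows only that no active enquiry or instruction is stated for them.
- **Other information.** Seriousness, expectedness and causality are assessed for each event, and pain and fatigue are also measured on the same schedule in both arms (Table 3). This helps interpretation, although falls are not in Table 3 and causality assessment cannot act on events that were never recorded.
- **Dependence on recall.** With perfect recall there is no inflation. Hospital admissions and similar events are less likely to be forgotten than mild soreness.

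None of this makes the counts in the two groups comparable. The protocol collects events in both arms, and readers will set the two counts side by side.

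**Conclusion.** The unequal ascertainment is written into the protocol: up to nine enquiries and a reporting instruction in one arm, and one stated enquiry in the other. At equal true risk, the exercise arm may show more recorded events if mild events are under-recalled over eight weeks. It is tempting to say that equal risk *will* look like harm from exercise. The documents do not support that, because they give neither an event rate nor a recall figure.

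Under the assumptions above, the recorded-event ratio at full attendance runs from 1.33 (half-life 8 weeks) to 2.50 (2 weeks), is slightly lower at 70% attendance, and is 1.00 with perfect recall. The harm is confined to descriptive comparison of counts between groups. In an exploratory feasibility trial with no stated adverse-event test or threshold, this is a recommended change and not an essential one.

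**What to change.** 1. Put one identical, neutrally worded adverse-event item in the weekly email already sent to controls and in the weekly survey the intervention arm already completes.
2. Give both arms the same instruction to contact the team about any event.
3. Base any between-arm table on this common item and the week-8 question. List events elicited in class or volunteered separately.
4. If weekly collection in controls is not adopted, limit any between-arm comparison to the week-8 question and state the difference in ascertainment. This needs only a reporting rule, but earlier weekly prompting may still affect what intervention participants recall at week 8.

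The cost is one survey item linked to existing weekly contacts, some protocol wording, a small burden on controls and a few more events to log. Weekly prompting could also make controls more aware of symptoms and might influence their self-reported outcomes, hence the neutral wording. Some asymmetry would remain, because in-class questioning continues and response to the weekly item may differ by arm. The change has to be made before data collection to be of full use.
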